#### Sample size estimate / power calculations

The required sample size was calculated with G*Power (Version 3.1.9.2, Heinrich Heine University of Duesseldorf) [97]. The following input parameters were used to obtain small-sized test × group interaction effects: effect size (f = 0.15), type I error (α = 0.05), type II error (1-β = 0.95), number of groups (*n* = 4), number of measurements (*n* = 3), correlation between measurements (r = 0.60). Additionally, a dropout rate of 30% (i.e., 20% lost to follow-up; plus 10% deceased) was considered. Our analysis resulted in a total sample size of 513 participants (i.e., 171 per center with 42–43 participants allocated to each group).

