**Methods:**

A three-arm single-blinded multicenter RCT with a wait-list control group will be conducted in a sample of 513 individuals (needed according to power analysis) in three different regions in Germany. In each nursing home, one of three different intervention approaches will be delivered to participating residents for 12 weeks, twice a week for 45 min each: The *PROfit basic* group will perform functional strength, balance, flexibility, and walking exercises always at the same location, whereas the *PROfit plus* group changes the location three times while performing similar/the same exercises as the PROfit basic group. The *PROfit orientation* group receives navigation tasks in addition to the relocation during the intervention. Physical and cognitive functioning as well as psychological measures will be assessed in all study groups at baseline. Participants will then be randomized into either the intervention group or the wait-list control group. After 12 weeks, and after 24 weeks the measures will be repeated.

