### Trial design

Based on the existing research and the physical training recommendations mentioned above, a multicenter intervention study will be conducted, aiming to determine the feasibility and efficacy of three different exercise intervention programs for residents of nursing homes. The type of intervention program will be randomly assigned to the participating nursing homes. The participants’ allocation to the intervention or wait-list control group will be randomized after baseline assessment in each nursing home. The assessment of primary and secondary outcomes will take place upon entry to the study (T1) by a blinded assessor and will be repeated at twelve (T2) and at 24 weeks (T3) (see Table 1).

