### Data collection, management, and analysis

#### Statistical analysis

Descriptive data will be reported as group mean values and standard deviations or medians and interquartile ranges depending on the type of outcome and their distribution. Analysis of baseline differences will be performed using a multivariate analysis of variance (MANOVA). Parametrical and normally distributed measures will be analyzed in separate 4 (group: PROfit basic, PROfit plus, PROfit orientation, wait-list control group) × 3 (test: baseline assessment, post-allocation, close-out-testing) analyses of variance (ANOVA) with repeated measures. If baseline differences are detected, baseline assessment values as well as age and sex discrepancies will be included as covariates in the statistical model. In the case of statistically significant interaction effects, Bonferroni-adjusted post-hoc tests (t-tests, Wilcoxon tests) will be performed to detect statistically significant differences in the groups between baseline- and post-allocation-testing. Kruskal-Wallis and Friedman tests instead of ANOVA will be used for non-parametrical variables and for data for which normal distribution could not be assumed. The effect size will be determined using Cohen’s *f* [95] which is indicative of the effectiveness of treatment and helps to assess whether a statistically significant difference is of practical concern. Cohen’s *f* values are classified as small (0 ≤ *f* ≤ 0.24), medium (0.25 ≤ *f* ≤ 0.39), or large (*f* ≥ 0.40). Additionally, PS_dep_ scores (probability of superiority for dependent samples) will be computed as an estimate of effect size in non-parametrical post-hoc tests [96]. The significance level will be set at *p* < 0.025.

Intention-to-treat analysis will be conducted. For this purpose, data of all participants will be processed in the groups into which they were randomly assigned, regardless of whether they received or adhered to the assigned intervention. The majority of participants are expected to take part in a minimum of 80% of the training sessions. An additional per-protocol analysis will be performed if a sufficient number of participants are lost to outcome assessment or insufficient participation in training sessions. Multiple Imputation will be used to handle missing data assuming that data are missing by chance.

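### The stated sample-size inputs do not lead to 513 participants, and the calculation uses alpha 0.05 while results are judged at 0.025

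*Protocol article*

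**What the plan says.** The section Sample size estimate / power calculations describes a G*Power calculation for a small test × group interaction. Its inputs are "effect size (f = 0.15), type I error (α = 0.05), type II error (1-β = 0.95", four groups, three measurements and a correlation of 0.60 between measurements. A 30% dropout rate is then allowed for, and the result is given as: "Our analysis resulted in a total sample size of 513 participants (i.e., 171 per center with 42–43 participants allocated to each group".

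The abstract repeats the number as a requirement: the trial "will be conducted in a sample of 513 individuals (needed according to power analysis").

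The Statistical analysis section plans the matching test, a 4 (group) × 3 (time) repeated-measures ANOVA, but adds: "The significance level will be set at *p* < 0.025".

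Under Trial design, each home is assigned one programme at random, and residents' "allocation to the intervention or wait-list control group will be randomized after baseline assessment in each nursing home". No allocation ratio is given in the text.

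**The concern.** The article gives every main input of a standard calculation, so a reader should be able to recover 513 from them. If that fails, the abstract's claim that the power analysis requires 513 has no support in the text, and nobody can tell whether the trial is much larger than its test needs or somewhat too small. Both remain possible, depending on what f = 0.15 means.

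The two significance levels are a separate inconsistency. A sample size computed at 0.05 says nothing direct about the power of a test judged at 0.025.

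**Working it through.** **Inputs.** From the sample-size section: f = 0.15, α = 0.05, 1−β = 0.95 (labelled type II error, read here as power), k = 4 groups, m = 3 measurements, r = 0.60, dropout 30%. From the Statistical analysis section: α = 0.025. Not stated, so assumed: sphericity (ε = 1; 0.5, the lowest value for three measurements, is also tried), equal groups and independent residents.

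**Formula with r.** For the within-between interaction, power comes from the noncentral F distribution with

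- λ = f²·N·m·ε/(1−r)
- df1 = (k−1)(m−1)·ε = 6 for ε = 1
- df2 = (N−k)(m−1)·ε = 2(N−4) for ε = 1

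**Attempt to reproduce 513 from the stated inputs, ε = 1, α = 0.05.**

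- N = 124: λ = 0.0225 × 124 × 3/0.4 = 20.9, power 0.945
- N = 127: power 0.950
- N = 128 (32 per group): λ = 21.6, power 0.952

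So 128 evaluable participants are needed in equal groups. Dividing by the retained fraction, 128/0.7 = 182.9, so 183 enrolled. The stated 513 is 513/183 = 2.8 times this.

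**Other readings.**

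| Reading | Evaluable | Enrolled (÷ 0.7) |
|---|---|---|
| Stated inputs, ε = 1, α = 0.05 | 128 | 183 |
| Same, ε = 0.5 | 208 | 298 |
| λ = f²·N·(m−1), which ignores r | 468 | 669 |
| Three times the per-centre figure | 384 | 549 |
| Stated inputs, ε = 1, α = 0.025 | 144 | 206 |

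None gives 513. The nearest is three times a per-centre calculation with dropout added as 30%: 3 × 128 × 1.3 = 499, or 3 × 167 = 501 if each centre is rounded up. That is not the inflation that leaves 128 completers after a 30% loss.

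**The per-centre figure itself.** 171 × 0.7 = 119.7, about 120 completers. With N = 120, λ = 20.25 and power is 0.937 at α = 0.05 and 0.893 at α = 0.025. On this reading too, 95% is not reached.

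**What 513 delivers overall.** 513 × 0.7 = 359 completers.

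- Convention with r: λ = 0.0225 × 359 × 3/0.4 = 60.6; power above 0.999 at either alpha.
- Convention without r: λ = 0.0225 × 359 × 2 = 16.2; power 0.87 at α = 0.05 and 0.80 at α = 0.025.

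**Group sizes.** 171/4 = 42.75, so 42–43 per group per centre means four equal groups, with wait-list controls making up a quarter. Each home contributes only its own programme and controls, so a common ratio across homes would have to be 3:1.

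**The case against.** The best defence is that the article hints at the derivation: by giving 171 per centre it suggests that each centre was sized separately and the result tripled. With dropout added as 30% this comes within 3% of 513, so the number may be undocumented rather than a slip. That is plausible, but it stays a guess. The text nowhere says the calculation was per centre, the planned ANOVA is not per centre, and 171 per centre still falls short of 95% power.

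It is also fair to say that the planned test is not left short. On the stated inputs even α = 0.025 needs only 206 enrolled. This stands, and it limits what the discrepancy means.

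Several stronger readings may tempt a reader and are not supported:

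- **The group sizes contradict the design.** They would under 1:1 within homes, which would give about 257 controls (513/2) and 86 per programme (513/6). But 1:1 is not stated, 3:1 would give the stated sizes, and the design and flow figures are not shown. The ratio is unstated in the text, not contradicted.
- **The 171 reveals a 25% loss allowance.** It is true that 128/0.75 = 170.7, but this works only from a base of 128; 171 fits 30% loss equally well from a base of 120.
- **The calculation is wrong because it ignores programme-versus-programme contrasts and clustering.** The calculation addresses the interaction test that the analysis section plans. Contrast-level power over a range of intracluster correlations would be a useful addition, but its absence is not an arithmetic error and an analysis plan could supply it.

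**Conclusion.** The concern holds for two things as written: 513 does not follow from the listed inputs under any of the readings above, and the sample size and the analysis use different alphas. Because the trial's stated size rests on this paragraph, it needs correcting.

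A reader might infer that the trial is underpowered. The article does not support that. With r entering the noncentrality, as its listing among the inputs suggests, 359 completers give over 99.9% power at 0.05 or 0.025. Only if f = 0.15 was meant in the convention without r does power fall below the stated 95%, to about 87% or 80%.

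Nor should 128 and 183 be taken as the single correct answer. They assume ε = 1 and the convention with r, and the article states neither. All these figures also assume equal groups, 30% loss and independent residents, and they concern only the omnibus interaction.

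**What to change.** Keep the enrolment target of 513 and restate the paragraph:

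1. State the effect-size convention and the epsilon used, and how 513 was obtained, including whether it is three times a per-centre figure and how dropout was applied.
2. Use one alpha in the sample-size and Statistical analysis sections.
3. Give the power that 359 completers provide for the 4 × 3 interaction at that alpha.
4. Amend the abstract so that it no longer presents 513 as required by the power analysis unless the restated derivation shows it.
5. State the within-home allocation ratio that produces 42–43 per group; four equal groups imply 3:1.

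The cost is rewording one paragraph and a phrase in the abstract, and aligning one alpha. No extra participants are needed. If f turns out to have been meant without r, the stated power will have to be lowered to about 87% or 80%, depending on the alpha kept.

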#### Monitoring

A data monitoring committee responsible for data monitoring, interim analyses, and auditing will be established. Project staff will intervene if negative reactions are observed during assessments and training interventions. Grant holders are part of a PROfit advisory board and responsible for data audits every 6 months.

## Discussion

The overall goal of this multicentric RCT is to determine the effects of three different cognitive-motor training interventions on PA, LS, and spatial orientation in a sample of nursing home residents. We expect slower declines or even improvements in PA, LS mobility, and spatial orientation in participants of all three groups compared to wait-list controls. Regarding the secondary outcomes, we expect that physical functioning, cognitive functioning, and psychosocial well-being will be improved in all residents participating in one of the three intervention arms, when compared to the wait-list control group.

The interventions of the PROfit program combine components of exercise programs that have been proven to yield health benefits for nursing home residents [51, 93, 98, 99]. Especially the physical outcomes, e.g., walking capacity, muscle strength, and balance capacity have been shown to be improved by multicomponent interventions as conducted within the PROfit approach [91, 93, 100].

However, regarding PA and LS, effectiveness has not yet been investigated. Therefore, we extended previous intervention approaches with changes of location during training and specific spatial orientation training to follow the principles of training and task specificity to increase the training effects. By adding different locations where the training is administered, we aim to increase physical, cognitive, orientation and psychosocial parameters substantially more with *PROfit plus* than with *PROfit basic.* Moreover, we expect the *PROfit orientation* intervention to be most effective due to its additional navigation and spatial orientation training components. We suppose that the effects of *PROfit orientation* on the primary outcomes will be reached via two mechanisms: (1) increased physical and cognitive performance will enhance cognitive-motor capacities and (2), according to Vance and colleagues the spatial training will help to build up cognitive strategies to compensate for age-related losses and limitations [64]. This, in turn, could translate into enhanced PA and LS due to better abilities to find the way, better knowledge of the nursing home building, alleys, floors, and room plans. One cognitive strategy would be the use of newly learned landmarks for an egocentric-based route strategy. Here, landmarks can be used as indicators where to turn in which direction to reach a specific goal location. Alternatively, landmarks can be integrated into an allocentric representation of the environment leading to improved knowledge of relative directions between different locations or even a survey-like representation of the environment. Introducing existing objects in and near the facility as landmarks for orientation reflects a compensatory approach [65] which in turn allows training of different spatial strategies based on this new information, eventually leading to improved spatial orienting abilities.

Overall, potential ways to encourage nursing home residents to participate actively in social life within the care setting are provided by facilitating a program that is appropriate and adapted to residents’ capacities, needs, and desires. Moreover, introducing a specific spatial cognitive component to the program and investigating the impact of nursing home facilities’ spatial structure and landmark availability, this program will allow to develop guidelines for interventions that specifically increase spatial orientation abilities in care home facilities and their contribution to general LS mobility and well-being. Results from this trial will particularly contribute to the evidence on motor-cognitive approaches in the maintenance of mental and physical functioning.

To this end, the findings may provide suggestions and support to handle present and future challenges, occurring at health promotion initiatives in the setting of long-term care, a sector that is highly relevant in times of aging populations in Western societies. With the prevention act of 2015, German health insurances have to provide preventive services in nursing homes. The multicentric RCT will show that universal prevention through motor exercise and spatial orientation training is possible and useful to improve health status and personal resources of nursing home residents.

## Data Availability

All participant information and data will be stored securely and identified by a coded ID number only to maintain participants’ confidentiality. It is planned to transfer the data to an open access repository.

## Abbreviations

ADL: Activities of daily living
BMI: Body Mass Index
COF: Concerns of falling
DIA-S: Depression in Age Scale
DRKS: German Clinical Trials Register
FITT: Frequency, intensity, time and type of exercise
GCP: Good Clinical Practice
IADL: Instrumental activities of daily living
IAGG: International Association of Gerontology and Geriatrics
LS: Life-space
Mini-BESTest: Mini Balance Evaluation Systems Test
MoCA: Montreal Cognitive Assessment
iTUG: Smartphone-based instrumented Timed Up and Go Test
NHLSD: Nursing Home Life-Space Diameter
PA: Physical Activity
PROfit: Prevention Orientation Training
RCT: Randomized controlled trial
SD: Standard deviation
Short FES-I: Short Falls Efficacy Scale international
SPIRIT: Standard Protocol Items: Recommendations for Interventional Trials
SPPB: Short Physical Performance Battery
SWLS: Satisfaction with Life Scale
